### Data management

Only persons who will be involved in the research project and identified will have access to the data entry software: OpenClinica. The data entry in the electronic case report form (e-CRF) will be controlled and formatted to prevent the entry of data out of bounds or outliers. In the event of an input change, traceability and activity tracking is ensured. An electronic signature committing the responsibility of the investigator of each center will allow the validation of the visit and the e-CRF. This software is hosted on a website within Nîmes University Hospital. Access to this application is secured and is via http://www.bespim.fr with a login and password. The data collected through this software is backed up daily on a secure network. The network is connected to the Internet and access is protected by a firewall.

The clinical data from the study will be stored on a specific server directory. Only network administrators and authorized persons in the Department of Biostatistics, Epidemiology, Clinical Research, and Health Economics may have access to this directory.

### Statistical analysis

Descriptive statistics will be reported as counts and percentages for categorical variables, means and standard deviations for continuous variables with normal distribution, and median and quartiles for others. Comparisons of baseline characteristics and of putative risk factors between the two periods will be performed. The primary outcome will assess the rate of patients having at least one preventable medication error through a mixed effect logistic regression model [40]. Let Y_ij_ be the *j*th observation (j = 1…m_i_) in the *i*th cluster (i = 1,2,…,K). The intervention variable is X_*i*_. The logistic mixed effect model is$$ \mathrm{Logit}\left({\mathrm{p}}_{\mathrm{i}\mathrm{j}}\right)={\upbeta}_0+{\upbeta \mathrm{X}}_{\mathrm{i}}+{\mathrm{Z}}_{\mathrm{i}} $$

Where Z_i_ is the random effect for cluster *i*, normally distributed with mean 0 and variance τ^2^, X_i_ is the group indicator. Therefore, the rate of patients having at least one preventable medication will be modeled as:$$ {\mathrm{p}}_{\mathrm{i}\mathrm{j}}=\mathrm{E}\left({\mathrm{Y}}_{\mathrm{i}\mathrm{j}}|{\mathrm{X}}_{\mathrm{i}},{\mathrm{Z}}_{\mathrm{i}}\right) $$

The other effects of putative predictors of the differences in medication adherence between patients from the control and the interventional periods will be evaluated. The secondary outcomes will be evaluated by descriptive and classical statistics: the acceptance rate of pharmaceutical interventions during the interventional period will be estimated (%) only in interventional period; the rate of readmission;, mortality at 30 and 90 days will be estimated and compared using a Chi-square test; the length of stay will be estimated and compared using a non-parametric test; and the descriptive statistics will be used to describe the results or the satisfaction of care providers.

The economic study proposed is in the form of a cost-consequence one, using the decision tree methodology. The decision tree is a decision support tool that uses a tree-like graph or model of decisions and their possible consequences, including chance event outcomes and/or resource costs. Each node of the tree is associated to a probability and each trajectory is associated to a leaf and a cost. A stochastic analysis will be performed. All probabilities will be associated to a beta distribution and 10,000 Monte Carlo simulations will estimate the mean cost and the associated confidence interval of each group (without vs with pharmacist). The robustness of the results will be checked with the sensitivity analysis. This will be done by performing a second estimation including a new set of parameters in the decision tree, in order to consider the uncertainty due to the sample, specifically on event probabilities and individual costs induced. If the results of global cost are unchanged, then the robustness could be deduced. The Tornado diagram will be used to evaluate and sort the most sensitive parameter.

The Department of Biostatistics, Epidemiology, Public Health, and Health Economics of Nîmes Hospital Center will perform the statistical analysis using R.4.0. (R Development Core Team [2017], R Foundation for Statistical Computing, Vienna, Austria; https://www.r-project.org) and TreeAge Pro 2017 (TreeAge Software, Williamstown, MA, USA; https://www.treeage.com).

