**Methods:**

This is a multicentric stepped wedge randomized study involving six care units from six French University Hospitals (each unit corresponding to a cluster) over seven consecutive 14-day periods. Each hospital unit will start with a control period and switch to an experimental period after a randomized number of 14-day periods. Patients aged at least 65 years hospitalized in one of the participating care units and having given their consent to be called for a 30-day and 90-day follow-up can be enrolled. For each 14-day period, 15 patients will be recruited in each care unit to obtain a total of 630 patients enrolled in all centers. Patients with a hospital stay of more than 21 days will be excluded. During the control period, there will be no clinical pharmacist in the care unit, whereas during the experimental period a clinical pharmacist will perform medication reconciliation and review with the healthcare team. The primary outcome will assess the impact of collaborative pharmaceutical care on preventable medication error rate. The secondary outcomes will evaluate the clinical impact of the strategy, the acceptance rate of pharmaceutical interventions, the induced and avoided costs of the strategy (cost-consequence analysis), and the healthcare team’s satisfaction.

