### Design

A multicentric stepped wedge cluster randomized trial is proposed because randomization of patients was not possible in this study due to the high risk of contamination bias. Indeed, once the clinical pharmacist arrives in the care unit, the collaborative pharmaceutical care will lead to change in medical practices for all the patients, including the control group. Stepped wedge randomized trial designs involve sequential roll-out of an intervention to participants over a number of time periods. By the end of the study, all participants will have received the intervention, although the order in which participants receive the intervention is determined at random. The clusters will be hospital units. Each hospital unit will start with a control period and switch to an interventional period. The study design will be composed of seven consecutive 14-day periods (Fig. 1). Every 14-day period, one further hospital unit will switch to the interventional period until all the units are in the interventional period in the final 14-day period. The randomization by the project methodologist will define the point that each hospital unit will switch from the control to the interventional periods (Table 1).

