### Sample size calculation

A stepped wedge trial was designed according to a validated methodology [39]. A previous study showed that the rate of patients with at least one medication error in the AMO was 46% and 2% for the control and experimental strategies, respectively [11]. In order to make more conservative assumptions, we decreased the expected difference from 0.44 to 0.30. The variance of the difference deducted was 0.20. The intra-class correlation coefficient was unknown but was assumed equal to 0.05 in the most conservative case. In each 14-day period, each investigator hospital center will recruit 15 patients, i.e. a total of 630 patients for the seven periods and the six hospital centers. These assumptions led to a statistical power estimated at 99% [39]. The required power was maximal in order to potentially perform subgroup analyses when justified.

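### With six clusters and only a unit random intercept, large-sample tests from the printed primary model can be anticonservative; period terms and a permutation test over the 720 switch orders would guard against this

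*Protocol article*

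**What the plan says.** The abstract describes a stepped wedge trial "involving six care units from six French University Hospitals (each unit corresponding to a cluster) over seven consecutive 14-day periods". The Design section adds the roll-out: "Every 14-day period, one further hospital unit will switch to the interventional period until all the units are in the interventional period". Table 1 confirms one unit per switch point, from period 2 to period 7, in units ranging from endocrinology and cardiology to geriatrics and emergency medicine.

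On the primary analysis, the Statistical analysis section states: "The primary outcome will assess the rate of patients having at least one preventable medication error through a mixed effect logistic regression model". The printed equation is logit(p_ij) = β0 + βX_i + Z_i, where Z_i is a normal unit intercept with variance τ². There is no term for calendar period, for unit-by-period variation, or for an effect that differs between units. X is indexed by unit alone, although every unit contributes both conditions; I read it as switching within the unit. The article names no test, reference distribution, small-sample correction or significance level.

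The Sample size calculation section says that "each investigator hospital center will recruit 15 patients, i.e. a total of 630 patients for the seven periods and the six hospital centers", takes an intra-class correlation (ICC) of 0.05 while calling it unknown, and concludes: "These assumptions led to a statistical power estimated at 99" per cent.

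**The concern.** A lone unit intercept says that two patients of one unit are equally correlated whether admitted in the same fortnight or three months apart, and that nothing changes over calendar time. Neither is argued for in the article. If unit error rates fluctuate from one 14-day period to the next, the model treats that fluctuation as patient-level noise. Its standard error is then too small. If error rates drift over the 14 weeks, the drift is confounded with the intervention, because intervention periods come later by design.

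Six units leave little information to correct for either. At stake is the calibration of the primary p-value and interval in an open trial that, according to the Discussion, is expected to feed professional recommendations.

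**Working it through.** **Inputs from the article.** Six units, seven periods, 15 patients per unit and period (6 × 7 × 15 = 630); difference 0.30; variance 0.20; ICC 0.05. The source study's rates are given as "the rate of patients with at least one medication error in the AMO was 46% and 2% for the control and experimental strategies, respectively", and then "we decreased the expected difference from 0.44 to 0.30".

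**Assumptions, not in the article.** Two-sided 5% level; control rate stays at 0.46, so the design difference is 46% versus 16%; variance 0.20 read as the individual-level variance. The between/within-period correlation ratios, trends and effect heterogeneity used below are also assumed.

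**Step 1: the stated power.** The standard stepped-wedge variance formula, which allows for period effects, is

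Var = Iσ²(σ² + Tτ²) / [(IU − W)σ² + (U² + ITU − TW − IV)τ²].

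I = 6, T = 7, U = 6+5+4+3+2+1 = 21, W = V = 91. σ² = 0.20/15 = 0.01333; τ² = 0.20 × 0.05/0.95 = 0.01053.

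- Numerator: 6 × 0.01333 × (0.01333 + 0.07368) = 0.00696.
- Denominator: 35 × 0.01333 + 140 × 0.01053 = 1.940.
- SE = √0.00359 = 0.0599; 0.30/0.0599 − 1.96 = 3.05; power 99.9%.

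Reading 0.20 as the total variance gives SE 0.058 and the same power. The stated 99% is reproduced within one point.

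**Step 2: size with no effect.** There were 5,000 simulated trials per scenario (Monte Carlo SE √(0.05 × 0.95/5000) = 0.3 points). The logistic random-intercept model was fitted by maximum likelihood, as printed and with fixed period effects. ICC 0.05 was represented by a logit SD of 0.45, since 0.46 × 0.54 × 0.45² = 0.050. For ratio 0.8 that SD was split into unit 0.45√0.8 = 0.40 and unit-period 0.45√0.2 = 0.20; for ratio 0.5, 0.32 each. The permutation test used a period-adjusted generalised least squares estimate on unit-period proportions, over all 6! = 720 orders. The two model columns are Wald z; likelihood-ratio results were within 0.3 points.

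| Scenario (no average effect) | As printed | With period terms | Permutation |
|---|---|---|---|
| Intercept only, ICC 0.05, rate 0.46 | 5.0% | 6.0% | 4.9% |
| Intercept only, ICC 0.05, rate 0.31 | 5.5% | 6.4% | 5.0% |
| Intercept only, ICC 0.01 | 5.7% | 6.7% | 5.3% |
| Intercept only, ICC 0.10 | 5.5% | 6.1% | 5.2% |
| ICC 0.05, ratio 0.8 | 6.9% | 7.6% | 4.8% |
| ICC 0.05, ratio 0.5 | 9.1% | 9.6% | 5.0% |
| ICC 0.10, ratio 0.8 | 9.2% | 9.8% | 5.5% |
| ICC 0.10, ratio 0.5 | 13.7% | 14.4% | 5.0% |
| Trend −0.25 logit | 12.1% | 6.6% | 5.3% |
| Trend −0.5 logit | 30.3% | 5.7% | 5.1% |
| Effect SD between units 0.2 logit | 8.4% | 8.5% | 6.2% |
| Effect SD 0.3 | 11.2% | 9.5% | 6.6% |
| Effect SD 0.45 | 16.2% | 10.8% | 7.5% |

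Two further sets of 3,000 trials gave, with period terms, 6.7% and about 7-8% for constant correlation, 7.5% and about 8% at ratio 0.8, and 10.1% and about 10% at ratio 0.5. A t reference with 4 degrees of freedom overcorrects: 0.7-3.6% in the scenarios without trend or heterogeneity.

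**Step 3: power of the permutation test against the period-adjusted Wald test.**

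| Difference | Wald z | Permutation |
|---|---|---|
| 0.30, constant correlation | 99.8% | 99.5% |
| 0.30, ratio 0.8 | 99.7% | 99.3% |
| 0.30, ratio 0.5 | 99.6% | 98.8% |
| 0.30, ICC 0.10, ratio 0.5 | 98.6% | 94.7% |
| 0.20, constant correlation | 86.5% | 82.8% |
| 0.20, ratio 0.8 | 85.9% | 78.5% |
| 0.15, constant correlation | 62.1% | 56.6% |

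ICC is 0.05 unless shown. A further set of 3,000 trials gave permutation power of 99.7%, 99.3% and 98.1% for the first three rows.

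**The case against.** **No test is named.** The choice of Wald, likelihood-ratio or small-sample reference may sit in an analysis plan that is not shown. This stands: a reader might infer that the trial commits to uncorrected large-sample tests, and the text does not say so. What the article does fix is the model's structure. The sentence promising to examine other predictors does not mention calendar period.

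**Six clusters alone do little harm.** A reader might infer that the small number of units by itself invalidates the test. The figures do not support that. On data of the kind the protocol assumes, the printed model has size 5.0-5.7%, because each unit crosses over and the effect is estimated largely within units. The larger inflation comes from omitted terms whose size the article does not give.

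**The permutation test has limits.** It is exact only under the strong null of no effect in any unit. With effects that differ between units around a zero average, its size is 6.2-7.5% with period adjustment and up to 9.5% without, lower than the corresponding model's but not nominal. The near-absence of a power cost at 0.30 is also a ceiling effect. At smaller differences the loss is real, although part of the Wald test's advantage is its inflated size. This matters because the sample size section wants power in hand for subgroup analyses.

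**What was not simulated.** The size of the model with a unit-by-period random effect was not checked, so these figures do not show that the permutation p-value would still be needed once that term is in.

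**Conclusion.** The point holds as a conditional one. The printed model omits period and unit-by-period terms, and large-sample tests from it can reject too often:

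- about 5-6% as printed if its assumption is exactly right;
- about 6-8% with period terms added;
- about 7-10% at ICC 0.05 with assumed correlation ratios of 0.8 and 0.5;
- about 30% as printed under an assumed −0.5 logit trend.

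The missing period term is the largest exposure, and adding it brings the trend scenarios back to about 6-7%. The residual inflation is moderate and depends on variation that the article leaves unquantified. It is plausible given the mix of specialties and the error detection done by each centre's own pharmacists. A reader might also infer that the 99% power claim is wrong; the recalculation gives 99.9%, so it is not. This is a worthwhile and inexpensive improvement, not a flaw that undermines the trial.

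**What to change.** Write the primary model with fixed effects for the seven periods, an intervention indicator indexed by unit and period, a unit random intercept and a unit-by-period random effect. Take the primary p-value from a period-adjusted permutation test over the 720 switch orders, using the weighted unit-period estimate as statistic, and report the model-based estimate and interval alongside. State the significance level, and confirm that all 720 orders were equally likely at randomisation, since the test relies on it. Note in the plan that the test is exact only under no effect in any unit.

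Trial status reports 622 patients already enrolled, so the change concerns analysis only and should be dated before the primary outcome is analysed.

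The cost is some extra computation and a slightly wider interval. Power at 0.30 stays about 98-99% with ICC 0.05 (94.7% with ICC 0.10 and ratio 0.5). With constant correlation, the loss against the period-adjusted Wald test is 86.5 − 82.8 = 3.7 points at 0.20 and 62.1 − 56.6 = 5.5 points at 0.15; at 0.20 with ratio 0.8 it is 85.9 − 78.5 = 7.4 points. The smallest attainable p-value is about 1/720 = 0.0014, ample for a 5% test. The stated power needs no correction.

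### The primary stepped wedge model has no period effect and indexes the intervention by unit only, so part of any calendar trend is reported as an intervention effect

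*Protocol article*

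**What the plan says.** The Design section describes a standard stepped wedge: "The study design will be composed of seven consecutive 14-day periods", and "Each hospital unit will start with a control period and switch to an interventional period". The roll-out is one unit at a time: "Every 14-day period, one further hospital unit will switch to the interventional period until all the units are in the interventional period". Table 1 gives the intervention starts as periods 2 to 7, one unit each.

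The Statistical analysis section specifies the primary analysis as an explicit equation: logit(p_ij) = β0 + βX_i + Z_i. The index j runs over patients in unit i, Z_i is a normal random intercept for the unit, and "X_i_ is the group indicator". No period index or period term appears. The only further covariates mentioned there are possible predictors of medication adherence, and calendar period is not named among them. No other section adds it.

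**The concern.** The printed equation is the model for a parallel cluster trial, in which each cluster stays in one arm. Here every unit contributes patients under both conditions, so an indicator that carries only the unit subscript cannot describe exposure.

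The missing period effect matters more. Period 1 is all control, period 7 is all intervention, and the exposed share rises steadily in between. Randomizing the order of switching does not break that link with time; only adjustment for time in the analysis does. Seven periods of 14 days span 98 days. Over that time case mix, staffing, prescribing habits or season could shift the error rate independently of the pharmacist. Without a period term, part of such a shift is credited to pharmaceutical care, or subtracted from it, in the primary estimate, confidence interval and p-value.

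**Working it through.** **Inputs.** From Design and Table 1: I = 6 units, T = 7 periods, switches at periods 2 to 7. From Sample size calculation: 15 patients per unit and period (6 × 7 × 15 = 630), difference 0.30, variance 0.20, intra-class correlation 0.05, stated power 99%. The article gives no alpha; two-sided 0.05 is assumed. Reading 0.20 as total variance gives τ² = 0.05 × 0.20 = 0.010 between units and 0.190 within, so the variance of a cell mean given its unit is σ² = 0.190/15 = 0.01267.

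**Design sums.** With X_it = 1 once unit i has switched: U = ΣX = 21; W = sum of squared period totals = 0+1+4+9+16+25+36 = 91; V = sum of squared unit totals = 36+25+16+9+4+1 = 91.

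**1. The plan's own power, with period effects.** The Hussey-Hughes variance is

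Var = Iσ²(σ² + Tτ²) / [(IU − W)σ² + (U² + ITU − TW − IV)τ²]

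- Numerator: 6 × 0.01267 × (0.01267 + 0.070) = 0.00628.
- Denominator: (126 − 91) × 0.01267 + (441 + 882 − 637 − 546) × 0.010 = 0.443 + 1.400 = 1.843.
- Var = 0.00341, SE = 0.0584.
- Power = Φ(0.30/0.0584 − 1.96) = Φ(3.18) = 99.9%.

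The stated 99% is reproduced. Reading 0.20 as within-unit variance gives SE 0.0599 and still 99.9%.

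**2. The same design without period effects.** Let c = τ²/(σ² + Tτ²) = 0.010/0.08267 = 0.1210, so that 1 − cT = 0.1532. The information on β is

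[(U − cV) − U²(1 − cT)/(IT)]/σ² = [(21 − 11.008) − 441 × 0.1532/42]/0.01267 = 8.383/0.01267 = 661.8

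so SE = 0.0389. The printed model therefore looks more precise by a factor of 0.0584/0.0389 = 1.50, but only by assuming that there is no time trend.

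**3. Imbalance in time.**
- Mean period of control cells: (1×6 + 2×5 + 3×4 + 4×3 + 5×2 + 6×1)/21 = 56/21 = 2.67.
- Mean period of intervention cells: 112/21 = 5.33.
- Gap: 2.67 periods × 14 days, about 37 days.

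**4. Bias from a linear drift of d per period, no true effect.** Projecting d(t − 1) onto the model without period gives

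bias = d × [(91 − c × 441) − ½ × 126 × (1 − cT)]/8.383 = d × (37.65 − 9.65)/8.383 = 3.34d

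The total change over the trial is 6d, so 3.34/6 = 56% of it enters the estimate. With fixed period effects the bias is zero.

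**5. False rejection.** The drift sizes are assumptions, shown as a range. The normal approximation uses SE 0.0389. The simulation column is a logistic random-intercept model with a 46% starting rate and 4,000 trials per row.

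| Drift per period | Bias | Normal approximation, no period | Simulation, no period | Simulation, with period |
|---|---|---|---|---|
| 0 | 0 | 5% | 5.4% | 6.2% |
| −1 point | −3.3 points | 14% | 11.7% | 6.4% |
| −2 points | −6.7 points | 40% | 32.7% | 6.9% |
| −3 points | −10.0 points | 73% | 61.4% | 7.0% |

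The simulated rates are lower in part because a 46% rate has binomial variance 0.46 × 0.54 = 0.248, above the plan's 0.20.

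A second, smaller simulation (250 trials per scenario, drift on the logit scale, true odds ratio 1) agrees:
- Drift from 46% to 36%: mean odds ratio 0.79 and 28% rejection without period; 0.98 and 8% with it.
- Drift from 46% to 26%: 0.61 and 76% without; 0.97 and 9% with.

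**6. Power at smaller differences, with period versus without.** 0.20: 92.9% versus 99.9%. 0.15: 72.9% versus 97.1%. 0.10: 40.2% versus 73.0%.

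**The case against.** Five points can be made for the plan.

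- **The bias is conditional and partial.** With no trend, the printed model (with exposure allowed to vary over time) holds its level: 5.4% in the larger simulation. A linear trend enters at 56% of its total change, not in full. The documents give no trend, and drifts of 2 or 3 points per period mean 12 or 18 points in about 14 weeks. All of this stands and limits how the result should be stated. It does not justify relying on an assumption of no trend that the article neither states nor defends.
- **At the planned effect the test decision hardly changes.** An adverse drift of 3 points per period leaves 0.30 − 0.10 = 0.20, and 0.20/0.0389 = 5.1, the same z as 0.30/0.0584 = 5.1 from the adjusted model. This is correct. The harm lies in a biased estimate and interval, and in false positives when the true effect is small.
- **The subscript on X may be a slip.** That is likely, since the Design section says that every unit switches. Correcting the subscript alone would still leave no period effect.
- **This could be left to the analysis plan.** The article prints the complete equation, so the model is stated, not deferred.
- **Six clusters are few for the adjusted model.** The Wald test with period effects rejects 6–7% in the larger simulation and 8–9% in the smaller one (Monte Carlo error about 2 points). This is a real but separate and smaller problem.

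**Conclusion.** The concern holds. The primary model as written does not fit the design: it has no period effect although exposure rises from none to all of the units over the seven periods, and its intervention term cannot vary within a unit. Under the plan's variance and intra-class correlation, a linear drift produces a spurious effect of 3.34 times the per-period change. Actual type I error depends on the size of the drift. For assumed falls of 1 to 3 points per period it is about 12–14% to 61–73%, depending on the method. These figures assume two-sided alpha 0.05, a linear trend common to all units, and 15 patients in every cell. The direction does not depend on those choices: without a period term, the analysis cannot separate pharmaceutical care from the passage of time.

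**What to change.** Replace the primary model by logit(p_ijt) = β0 + γ_t + βX_it + Z_i, with a fixed effect γ_t for each of the seven periods (one as reference) and X_it = 1 from the period in which unit i switches. Make it the single primary analysis. As a separate point, state which small-sample correction will be used for six clusters.

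The cost is a wider interval: SE about 0.058 instead of 0.039 on the risk-difference scale. No extra patients are needed, because power at 0.30 remains 99.9%. Subgroup analyses, or a true effect below about 0.20, would have clearly less power than the unadjusted model suggests. Trial conduct does not change. Since Trial status reports 622 of the planned 630 patients already enrolled, the change should be a dated, documented amendment made before any outcome comparison is run.
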